### Sample size justification

A previous pilot trial in Shuguang Hospital used comprehensive scores of abdominal ultrasounds to evaluate efficacy. The score includes the evaluation of 7 indicators such as liver shape, contour, echo, and vascular structure. Each indicator is divided into 4 grades: normal, mild, moderate, and severely abnormal. Twenty-six patients (65%) experienced a 1-grade or more decrease in at least 3 indicators after treatment with JPHX compared to baseline [27, 29]. In this trial, a 26% relative reduction from baseline in liver MRI-PDFF will be expected in 60% of JPHX-treated cases compared to 30% in the placebo control group. Assuming *α* = 0.05, *β* = 0.2, *π*_*T*_ = 0.6, *π*_*C*_ = 0.3, *δ* = 0.01, *n*_*T*_ : *n*_*C*_ = 1:1. According to the optimal sample size calculation formula, each group will get 33 samples. Considering the dropout rate of 20%, a minimum of 42 individuals will be obtained per group.$${\mathrm{n}}_{\mathrm{T}}={\mathrm{n}}_{\mathrm{C}}=\frac{{\left({z}_{1-\alpha }+{z}_{1-\beta}\right)}^2\left[{\pi}_T\left(1-{\pi}_T\right)+{\pi}_C\left(1-{\pi}_C\right)\right]}{{\left[\left({\pi}_T-{\pi}_C\right)-\delta \right]}^2}$$

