**Methods:**

This is a randomized, double-blind, placebo-controlled clinical trial. The trial will enrol 84 NAFLD participants who will be equally randomized to receive either JPHX or a placebo for 24 weeks. Follow-up will be performed 12 weeks after the intervention. The primary outcome will be the change from baseline to week 24 in MRI-PDFF. Secondary outcomes will be the body weight, body mass index (BMI), waist circumference, waist-to-hip ratio (WHR), serum liver function, blood lipids and glucose-related indicators, quality of life measurement health survey, and traditional Chinese medicine (TCM) syndrome scale. Outcomes will be monitored at baseline, 12 weeks and 24 weeks after enrolment. Adverse events occurring in this trial will be managed and recorded promptly.

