### Outcomes

The primary outcome is the relative change of MRI-PDFF from baseline to 24 weeks.

The secondary outcomes include changes in ① body weight, body mass index (BMI), waist-to-hip ratio (WHR); ② serum liver function including total bilirubin (TBIL), direct bilirubin (DBIL), indirect bilirubin (IDBIL), ALT, aspartate aminotransferase (AST) [16], gamma-glutamyl transpeptidase (GGT), alkaline phosphatase (ALP), albumin (ALB) [28], pre-albumin (Pre-ALB), and total bile acid (TBA); ③ fasting serum lipids; ④ blood glucose-related indicators, such as fasting plasma glucose (FPG), fasting insulin (FINS), and Homeostasis model assessment – insulin resistance (HOMA-IR). All mentioned serum biochemical markers will be measured at baseline, 12 weeks and 24 weeks after randomization. ⑤ Health related quality of life (SF-36). ⑥ Chronic Liver Disease Questionnaire (CLDQ), ⑦ TCM Syndrome Score Scale (TCMSSS).

Blood routine, urine routine, blood urea nitrogen, creatinine, uric acid, and SAEs are included as safety outcomes in this trial.

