### Randomization and concealment

#### Allocation

Enrolled participants will be randomized 1:1 to either the JPHX group or the placebo control group according to a randomization sequence designed by an external statistician using SPSS software (Version 24.0). The sequence will be sealed in opaque envelopes and kept independently as confidential documents.

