Considering that it is difficult to perform liver biopsies in fatty liver clinical practice, this trial used the relative change in MRI-PDFF from baseline as the primary outcome. MRI-PDFF is a new MRI technique with more accurate performance than CAP in the non-invasive diagnosis of hepatic steatosis in NAFLD patients [40]. There is a significant correlation between MRI-PDFF values in NAFLD patients and steatosis grades determined by invasive histologic examination [41]. The cut-off criteria for MRI-PDFF to correspond to NAFLD pathological grading are unclear, and MRI-PDFF ≥ 5% or hepatic steatosis ≥ 5% on liver biopsy are commonly used as diagnostic criteria for fatty liver disease [42]. Loomba's study [3] found an absolute decrease of 4.8% or a relative decrease of 26% in MRI-PDFF from baseline was associated with a 1-grade improvement in hepatic steatosis on liver biopsy. Based on this, we used MRI-PDFF <5% at week 24 post-enrolment as the recovery criterion and a 4.8% absolute or 26% relative decrease in MRI-PDFF from baseline as improvement in hepatic steatosis. The liver function, blood lipids and glucose, BMI, waist-hip circumference, and SF-36 score will also be observed as the effects of JPHX on NAFLD patients.

In conclusion, this is a randomized, double-blind, placebo-controlled clinical trial to evaluate the efficacy and safety of JPHX for NAFLD patients. The findings of this trial may provide evidence for a rigorous, large-scale, confirmatory RCT to confirm the efficacy and safety of JPHX for the administration of patients with NAFLD.

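### The sample size is a power calculation for a 26% responder proportion, but the declared primary outcome is the continuous relative change in MRI-PDFF, so the stated 80% power does not describe the primary analysis

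*Protocol article*

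**What the plan says.** The Outcomes section of the protocol article fixes the primary: "The primary outcome is the relative change of MRI-PDFF from baseline to 24 weeks". The Discussion repeats that relative change is the primary outcome. The abstract is looser: "The primary outcome will be the change from baseline to week 24 in MRI-PDFF". None of these gives a threshold.

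The Statistical analysis section compares continuous variables between groups with an independent t test or a Wilcoxon rank-sum test and makes all tests two-sided. Its line on chi-square and Fisher tests is general and names no MRI-PDFF endpoint.

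The Sample size justification section works with proportions. It says that "a 26% relative reduction from baseline in liver MRI-PDFF will be expected in 60% of JPHX-treated cases", "compared to 30% in the placebo control group". It takes a significance level of 0.05, β = 0.2 and δ = 0.01, and concludes that "each group will get 33 samples", raised to 42 for 20% dropout. It states no mean difference and no SD for relative change.

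The Discussion also takes "a 4.8% absolute or 26% relative decrease in MRI-PDFF from baseline as improvement in hepatic steatosis". It presents this as a criterion of improvement, not as the primary outcome.

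**The concern.** A sample-size paragraph should tell the reader what chance the primary analysis has of detecting the effect the trial was designed for. Here it gives that chance for a comparison of responder rates, which is neither the declared primary nor a listed secondary outcome. A reader who takes the 80% as the power of the primary analysis is misled. When the result comes in, nothing in the document says what difference in relative change the trial was built to detect.

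The responder event is also unsettled. The sample-size section requires a 26% relative fall; the Discussion accepts either that or a 4.8-point absolute fall. If a responder analysis is reported, the two sections support different counts.

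**Working it through.** **1. Reproduce the stated figure.** Inputs from the Sample size justification section: π_T = 0.6, π_C = 0.3, α = 0.05 entered as z(1−α) = 1.645, z(1−β) = 0.842, δ = 0.01, equal groups.

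- Variance term: 0.6 × 0.4 + 0.3 × 0.7 = 0.45
- n = (1.645 + 0.842)² × 0.45 / (0.30 − 0.01)² = 33.08 per group (unrounded z values)
- With dropout: 33 / 0.8 = 41.25, hence 42 per group and 84 in total

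The plan reports 33; strict rounding up would give 34, a trivial difference. The figure therefore reproduces as a one-sided two-proportion calculation. Power at n = 33 under that formula is 79.9%.

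**2. Is the sized event a listed outcome?** The Outcomes section and the abstract list no MRI-PDFF responder proportion, primary or secondary. The only other threshold is the one in the Discussion, and it is a different event. A fall of 4.8 points is less than 26% of baseline whenever baseline exceeds 4.8 / 0.26 = 18.5%. A patient going from 25% to 20% falls by 5 points but only by 5/25 = 20%. That patient is improved under the Discussion and a non-responder under the sample-size section. The 60% and 30% rates cannot be carried over from one definition to the other.

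**3. What 33 per group gives for the declared outcome.** The calculation is a two-sample t test, two-sided 0.05. The smallest difference detectable with 80% power is 0.70 SD (normal approximation: (1.960 + 0.842) × √(2/33) = 0.69).

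Power needs a mean difference and an SD, and the documents give neither. Two sets of assumptions show the range.

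*(a) Normal shift.* If relative change is normal with the same SD in both arms, 60% v 30% below one cut-point implies a difference of z(0.6) − z(0.3) = 0.253 + 0.524 = 0.778 SD. Power of the t test at 33 per group is 87.5%.

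*(b) An assumed mean difference of 20 percentage points in relative change:*

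| Assumed SD (points) | Difference in SD units | Power, 33 per group |
|---|---|---|
| 20 | 1.00 | 98% |
| 30 | 0.67 | 76% |
| 40 | 0.50 | 52% |

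In points, 0.70 SD is 14, 21 or 28 at those SDs.

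**The case against.** The strongest defence is that the primary outcome is not in doubt. Outcomes and Discussion agree on relative change, the abstract's wording is a less specific form of the same variable, and the Discussion's composite criterion is never called primary. That stands. A reader might infer that several rival primaries are open, so that one could be chosen after the data are seen and the false-positive rate inflated. The documents do not support this: the declared primary is consistent, and no passage offers the responder proportion as an alternative primary test.

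A second defence is that sizing on a dichotomised outcome is conservative, because the continuous test usually has more power. Under assumption (a) that is so: 87.5% exceeds the stated 80%. But it depends on a normal shift that the plan neither states nor supports, and assumption (b) shows that power can fall well below 80%. The defence removes any claim of demonstrated underpowering; it does not make the stated power apply to the primary test.

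A reader might also set the 87.5% against the power of the two-sided responder comparison with 33 per group (about 70% by the normal approximation, 73.6% exact for chi-square) and call the whole gap the cost of the mismatch. That overstates it. The gap rests on assumption (a), and the drop from 80% to about 70% comes from the formula's one-sided z against a two-sided analysis, which is a separate matter.

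An unseen analysis plan could add detail, but it could not turn the printed calculation into one for the declared outcome. Both statements are in this article, and they disagree.

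**Conclusion.** The point holds as a mismatch between the sized endpoint and the declared endpoint. The arithmetic for 33 is sound on its own terms. The error is to present its 80% as the power of a trial whose primary analysis is a two-sided comparison of a continuous variable.

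The size of the effect on power cannot be fixed from the documents: about 87% under the normal-shift assumption, and from 98% down to 52% for an assumed 20-point difference with SD between 20 and 40 points. Neither adequate nor inadequate power is shown. The 0.70 SD figure says what the existing number can detect; it does not by itself justify that number.

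The correction should be made before unblinding, because it concerns the stated basis of the primary analysis and costs little.

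**What to change.** 1. Keep relative change in MRI-PDFF from baseline to week 24 as the single primary outcome, and add the word relative to the abstract.
2. List the responder proportion as a named secondary outcome with one definition and its test. Reconcile the 26% criterion in the sample-size section with the two-limb criterion in the Discussion.
3. Rewrite the sample-size paragraph for the continuous outcome. It should say that 33 evaluable per group gives 80% power at two-sided 0.05 for a difference of 0.70 SD, state the mean difference and SD assumed for relative change with their source, and give the power that follows.

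The cost is protocol wording, with ethics re-approval as the Ethical consideration section requires for modifications. The planned 84 can stay, provided the power is restated to whatever the assumptions deliver, even if that is below 80%.

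Making the responder proportion primary instead would also remove the mismatch, but it is dearer. The printed formula with a two-sided z gives 42.0 evaluable per group, and 42 / 0.8 = 52.5, hence 53 per group or 106 in total.

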### Statistical analysis

Statistical analysis will be performed by an independent researcher. The primary outcome efficacy evaluation will be conducted in the full analysis set [35] according to the intention-to-treatment (ITT) principle. Cases that met the trial protocol had good compliance (> 80%), did not take illicit drugs during the trial, and completed the contents of the CRF regulations will be defined as the Per-Protocol Set. The missing data will be replaced using the last observation carried forward (LOCF) method.

Continuous data will be described using mean ± standard deviation or median (range) depending on the distribution of the data. Comparison of mean or median values of continuous variables from the two groups will be undertaken using an independent *t* test or Wilcoxon rank-sum test. Paired *t* test or Wilcoxon signed-rank test will be used to compare the distribution of pre- and post-treatment changes within each group. Categorical data will be described by frequency counts and constituent ratio and will be compared using the chi-square test/Fisher exact test. All statistical analyses will be conducted with the bilateral test, and *P* value less than or equal to 0.05 will be considered statistically significant. Subgroup analyses will be performed based on information collected to explore the source of potential high heterogeneity.

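### The sample size rests on a one-sided 5% critical value while all tests are two-sided at 0.05, so 33 evaluable per group gives about 70–74% power by chi-square for 60% v 30% responders, not the stated 80%

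*Protocol article*

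**What the plan says.** The protocol article, section Sample size justification, opens its calculation with "Assuming *α* = 0.05, *β* = 0.2" and a margin δ of 0.01. A responder is a patient with a 26% relative fall in MRI-PDFF, and response "will be expected in 60% of JPHX-treated cases compared to 30% in the placebo control group". The formula printed there adds z(1−α), not z(1−α/2), to z(1−β). It then states: "According to the optimal sample size calculation formula, each group will get 33 samples", and "Considering the dropout rate of 20%, a minimum of 42 individuals will be obtained per group". The abstract gives the resulting total: "The trial will enrol 84 NAFLD participants who will be equally randomized".

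The section Statistical analysis fixes the tests: "All statistical analyses will be conducted with the bilateral test, and *P* value less than or equal to 0.05 will be considered statistically significant". It names the chi-square or Fisher exact test for categorical data and the t test or Wilcoxon rank-sum test for continuous data. No section declares a one-sided primary test or a test against a 0.01 margin.

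**The concern.** The planning formula and the planned test use different critical values for the same α. Sizing with 1.645 and testing at 1.960 gives a trial with less power than stated. β = 0.2 is the article's justification for 84 participants, and readers will use it to judge a non-significant result. If the true chance of missing a 60% v 30% difference is nearer 26–30% than 20%, the justification is wrong for the comparison it describes.

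The article prints both sides of the conflict, so this is not a detail left to a separate analysis plan.

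**Working it through.** **Inputs.** From Sample size justification: α = 0.05, β = 0.2, π_T = 0.6, π_C = 0.3, δ = 0.01, 1:1 allocation, 20% dropout. From Statistical analysis: two-sided tests, P ≤ 0.05, chi-square or Fisher. Critical values (unrounded in the calculation): z(0.95) = 1.645, z(0.975) = 1.960, z(0.80) = 0.842.

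**1. Reproduce the plan's figure.** The article's formula is n = (z_α + z_β)² × [π_T(1−π_T) + π_C(1−π_C)] / [(π_T−π_C) − δ]².

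- Variance term: 0.6×0.4 + 0.3×0.7 = 0.24 + 0.21 = 0.45.
- Denominator: (0.30 − 0.01)² = 0.0841.
- With 1.645: n = 33.08, the stated 33.
- Dropout: 33/0.8 = 41.25, rounded up to 42 per group and 84 in total, as stated.

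**2. Put the planned two-sided test into the same formula.**

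| Critical value | δ | n evaluable per group | Randomised per group at 20% dropout | Total |
|---|---|---|---|---|
| 1.645 (as printed) | 0.01 | 33.08 | 42 (from 33) | 84 |
| 1.960 | 0.01 | 41.998, so 42 | 42/0.8 = 52.5, so 53 | 106 |
| 1.960 | 0 | 39.24, so 40 | 40/0.8 = 50 | 100 |

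The pooled-variance formula was also tried. It gives 33 one-sided and 42 two-sided. No two-sided variant tried gives 33.

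**3. Two-sided power with 33 evaluable per group.** The standard error is √(0.45/33) = 0.1168.

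- Unpooled, δ = 0.01: Φ(0.29/0.1168 − 1.960) = 70.0%.
- Unpooled, no margin: Φ(0.30/0.1168 − 1.960) = 72.9%.
- Pooled normal approximation: 69.6%.
- Exact enumeration of both binomials, uncorrected chi-square: 73.6%.
- Exact enumeration, Fisher: 64.6%.

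For comparison, the one-sided critical value with δ = 0.01 gives 79.9% at 33, which confirms where the stated 80% comes from.

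**4. Where 80% is reached, two-sided.**

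| Evaluable per group | Unpooled, δ = 0.01 | Unpooled, δ = 0 | Exact chi-square | Exact Fisher |
|---|---|---|---|---|
| 40 | 78.1% | 80.7% | 79.6% | 72.5% |
| 41 | 79.0% | 81.7% | 81.3% | 74.5% |
| 42 | 80.0% | 82.6% | 82.8% | 76.4% |

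About 40–42 evaluable per group are needed by chi-square. Fisher's test does not reach 80% even at 42.

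**The case against.** **The analysis is by intention to treat, so all 42 per group count.** The full analysis set with last observation carried forward keeps dropouts in the denominator. If 60% and 30% are rates among all randomised patients, n is 42 and two-sided power is 80.0% (with margin) to 82.6% (without). That is fair, and it shows that the 70–74% rests on reading 33 as the number evaluable, which is how the article itself uses it. But the section Study visit overview schedules MRI-PDFF only at weeks 0 and 24, so a patient without the second scan carries the baseline value forward and becomes a non-responder. If 20% per group are lost that way and 60% v 30% holds among those scanned (an assumption), the rates become 0.8×60% = 48% and 0.8×30% = 24%. Power at 42 per group is then 65% by exact chi-square and 56% by Fisher. Intention to treat does not by itself restore 80%.

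**A superiority-margin formula is naturally one-sided.** It is, but the planned test would then have to be one-sided against that margin. The article instead says: "All statistical analyses will be conducted with the bilateral test".

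**The primary outcome is continuous.** This stands as a limit. The section Outcomes defines it as the relative change in MRI-PDFF. A reader might infer that the trial has only about 70% power for its primary outcome. The article does not support that: it gives no mean difference or standard deviation, so that power is unknown and may be higher or lower.

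**Two further inferences fail.** A reader might conclude that 80% is reached only with zero dropout. That is so only by the normal approximations at exactly 42; without the margin, which no planned test uses, 40–41 evaluable of 42 suffice by chi-square. A reader might also object to rounding 33.08 down, but 33.08/0.8 = 41.35 still rounds up to 42, so nothing changes. The margin itself is mildly conservative: without it the one-sided n would be 30.9.

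**Conclusion.** The mismatch is real and explicit. The stated β = 0.2 is not delivered for the 60% v 30% responder comparison. At two-sided 0.05 with 33 evaluable per group, power is about 70–73% by normal approximation, 73.6% by exact chi-square and 64.6% by Fisher. The shortfall is therefore about 6 to 10 percentage points with chi-square and about 15 with Fisher.

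This rests on the article's own response rates and dropout, and on taking 33 as the number analysed. It does not extend to the continuous primary outcome. Nor does it show that 84 participants are too few for a trial that the Discussion presents as possible groundwork for a larger confirmatory one. It shows that the stated power for that number is wrong.

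**What to change.** Keep 84 participants and replace the derivation with a power statement, for example: with two-sided α of 0.05 and 60% v 30% responders, 33 evaluable per group give about 70–74% power by the chi-square test (about 65% by Fisher's exact test); about 80% by chi-square needs roughly 40–42 evaluable per group. Add that this refers to the responder comparison and not to the continuous primary outcome. Delete the 0.01 margin.

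Putting z(1−α/2) into the printed formula while leaving 33 and 42 in place would not do: the formula would then return 42 evaluable and 53 randomised per group (40 and 50 without the margin) and create a new contradiction.

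The change is to wording only. No participants, visits or tests change. The cost is a less favourable stated power.

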### Study visit overview

Five visits including one follow-up are designed in this trial: at 6, 12, 18, 24, and 36 weeks after enrolment. Each time point has 5 days of time flexibility. Participants will have their vital signs checked at each visit, receive health education and medication for the next 6 weeks, and return any remaining drugs from the previous visit. Other concomitant medications and their doses during this period will be recorded in the CRF. Compliance with the treatment will be evaluated by pack count at each visit and serious adverse events will be recorded. MRI-PDFF examinations will be performed at weeks 0 and 24, and laboratory indicators will be measured at weeks 0, 12, and 24. SF-36, CLDQ, and TCMSSS will be filled out at 0 and 24 weeks. The TCMSSS consists of 55 questions about conventional symptoms of TCM syndromes, and each symptom is divided into four grades according to its frequency or degree. These questions are derived from a Patient-Reported Outcome (PRO) questionnaire for patients with hepatitis B virus-related cirrhosis (PHBC-PRO) [33, 34] and are expanded to studies of TCM for the treatment of chronic liver diseases. TCM syndrome diagnosis and its related degree can be reflected according to the combination and degree of positive symptoms. Any questions raised by participants will be answered to facilitate completion. The study schedule is shown in Fig. 2.

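### The step from 33 to 42 per group keeps 80% power for the responder comparison only if dropouts leave it; under the stated ITT/LOCF rule and 20% dropout, responder-scale power is about 73%

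*Protocol article*

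**What the plan says.** **Sample size justification.** The target is a responder comparison: a 26% relative reduction in MRI-PDFF "will be expected in 60% of JPHX-treated cases compared to 30% in the placebo control group". The inputs are alpha 0.05, beta 0.2, a margin of 0.01 and equal allocation. The displayed formula uses the one-sided normal quantile for alpha. It yields 33 per group, followed by: "Considering the dropout rate of 20%, a minimum of 42 individuals will be obtained per group".

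**Statistical analysis.** The primary efficacy evaluation will be "conducted in the full analysis set [35] according to the intention-to-treatment (ITT) principle". On missing values: "The missing data will be replaced using the last observation carried forward (LOCF) method". On sidedness: "All statistical analyses will be conducted with the bilateral test".

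**Study visit overview.** "MRI-PDFF examinations will be performed at weeks 0 and 24". No scan is scheduled in between.

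**Outcomes.** The primary outcome is the relative change in MRI-PDFF from baseline to week 24, a continuous variable. The responder definition (26% relative or 4.8% absolute decrease) appears in the Discussion as a criterion of improvement.

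**The concern.** A dropout allowance of n/(1 − d) replaces lost headcount. It is right when dropouts vanish from the comparison and the remaining patients show the planned rates. It falls short when dropouts stay in the denominator and are given an outcome that cannot be a response, because the difference between groups then shrinks as well.

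Read together, three statements in the article point to the second situation. ITT with LOCF keeps dropouts in. With a single post-baseline scan, the only value to carry forward is the baseline scan. A relative change of 0% cannot meet a 26% reduction. The sample-size section restores the number of patients but takes no account of the smaller difference.

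What is at stake is how the stated beta is read. A responder result that misses significance in 84 patients would be judged against 80% power, which that comparison does not have under the plan's own dropout rate and missing-data rule. The point is separate from the one-sided formula and from the question of which imputation method is best.

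**Working it through.** **Inputs.** From the sample-size section: rates 0.60 and 0.30, margin δ = 0.01, one-sided alpha 0.05 (z = 1.645), beta 0.2 (z = 0.842), dropout 20%, 42 per group. From the other sections: ITT with LOCF, and MRI-PDFF at weeks 0 and 24 only.

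**1. The plan's own figures.**
- n = (1.645 + 0.842)² × (0.6×0.4 + 0.3×0.7) / (0.30 − 0.01)² = 6.183 × 0.45 / 0.0841 = 33.08, stated as 33.
- 33 / 0.8 = 41.25, so 42. Both figures reproduce.

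**2. Power if dropouts leave.** Inverting the same formula, power = Φ[(pT − pC − δ)/SE − z], with SE = √{[pT(1−pT) + pC(1−pC)]/n}.
- n = 33, 0.60 v 0.30: SE = √(0.45/33) = 0.1168; 0.29/0.1168 = 2.483; Φ(2.483 − 1.645) = 79.9%. This matches beta 0.2.

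**3. Power if unscanned dropouts stay with 0% change.**
- Analysed rates: 0.8 × 0.60 = 0.48 and 0.8 × 0.30 = 0.24. The difference falls from 30 to 24 points.
- Variance term: 0.48×0.52 + 0.24×0.76 = 0.432. SE at n = 42: √(0.432/42) = 0.1014.
- On the formula's terms: (0.24 − 0.01)/0.1014 = 2.268; Φ(2.268 − 1.645) = 73.3%.
- One-sided, no margin: 0.24/0.1014 = 2.366; Φ(2.366 − 1.645) = 76.5%.
- Two-sided, no margin: Φ(2.366 − 1.960) = 65.8%. An exact calculation for the two-sided chi-square test gives 65.1%.

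For comparison, 33 completers with a two-sided test and no margin have 72.9%. The loss from retained dropouts is thus about 7 points on either footing (79.9 to 73.3, or 72.9 to 65.8). It does not depend on the sidedness of alpha.

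**4. Sensitivity to the dropout rate** (42 per group, formula's terms, equal in both groups):

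| Dropout | Analysed rates | Power |
|---|---|---|
| 5% | 57% v 28.5% | 84.5% |
| 10% | 54% v 27% | 81.0% |
| 15% | 51% v 25.5% | 77.3% |
| 20% | 48% v 24% | 73.3% |

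The shortfall is present at the protocol's own 20%, but not at 10%. Unequal dropout averaging 20% moves the figure a good deal: 86.2% with 15% on JPHX and 25% on placebo, 56.7% with the reverse.

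**5. The continuous outcome.** The documents give no SD, so its power cannot be computed. As an illustration only, assume a normal relative change with a common SD, means set so that 60% v 30% reach a 26% reduction, and 20% of each group set to zero change. Simulated power of a two-sided t test with 42 per group is then about 71% for an SD of 15 percentage points, 79% for 20, 82–84% for 25–30 and 86% for 40.

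**The case against.** **The responder comparison is not the declared primary analysis.** This is the strongest objection, and it stands. The declared outcome is continuous and would be compared by t test or Wilcoxon test. A reader might infer from 73% that the primary analysis lacks 80% power, or that the trial never had the power it claims. The documents do not support that: zero-change imputation shrinks the mean difference too, but without an SD the power may fall on either side of 80%, as the illustration shows. The objection does not rescue the sample-size section, which states its beta on the responder scale and can be checked only there.

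**The full analysis set may exclude patients without a post-baseline scan.** The article does not define the set, cites a source for it, and never uses the word non-responder. If unscanned patients are excluded, about 33 per group remain and the step to 42 is right. This stands as a condition. Against it, the article names ITT together with a replacement rule, and with one post-baseline scan LOCF could never act on MRI-PDFF if those patients were removed.

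**60% and 30% may already be rates among all randomised patients.** The text speaks of treated cases, not completers. On that reading 42 per group give 87.6% on the formula's terms, but no dropout inflation would have been needed. Dividing by 0.8 implies completer rates, though the text does not say so.

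**Nothing is miscalculated.** Agreed: n/(1 − d) is customary, and 42 follows from 33. The fault is that this allowance does not fit the analysis set and missing-data rule stated in the same article.

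**Conclusion.** The point holds on the responder scale. The stated beta of 0.2 describes about 33 evaluable completers per group. Under the protocol's own 20% dropout and its ITT/LOCF rule, with scans only at weeks 0 and 24, responder-scale power with 42 per group is about 73% on the formula's terms, a type II error of about 0.27. With a two-sided test and no margin it is about 66%.

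This rests on three assumptions: 60% and 30% are completer rates; dropout is 20% in each group and dropouts have no week-24 scan; and unscanned patients stay in the full analysis set. The first and third are implied by the article but not stated.

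It does not show that the continuous primary comparison falls short of 80%. That power is unknown from this document.

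**What to change.** Amend the sample-size section in one or two sentences and leave enrolment at 84:

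- State that the 80% figure refers to the responder comparison in about 33 evaluable completers per group.
- Give the responder power in the full analysis set under the stated LOCF rule and 20% dropout: 48% v 24% with 42 per group, about 73% on the formula's terms or about 66% two-sided without margin. State the three assumptions with it.
- Say that neither figure is the power of the continuous primary comparison.

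The cost is a less favourable stated power. No patient number, outcome or analysis changes. The last sentence matters, because without it the added figures could be taken for the power of the primary outcome.
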